### Sample size

A goal of this pilot RCT is to estimate effect sizes for a full-scale RCT. Within the constraints of a pilot study, we aim to have reasonable power to detect a clinically meaningful effect for mechanisms of action (T2 adherence, coping) and child health outcomes (T3 physical recovery, HRQOL, emotional health symptoms). A sample of *n* = 80 (40 per condition; 68 [85%] retained to T3) can detect a 0.7 effect size between groups at T3 (ANCOVA) with 80% power and α = 0.05. Retention rate will be tracked and considered in designing subsequent research trials.

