### Data analysis

For all analyses, we will include covariates of child age, sex, and injury characteristics (e.g. severity, length of recovery, type of procedures). Missing data will be imputed in cases in which at least 50% of a measure’s subscale is complete; in cases in which > 50% of the items on a given subscale are missing, participants’ will be dropped from analyses requiring those subscales but will be retained in the overall study. Regarding the primary objective, examining intervention feasibility (fidelity, acceptability, implementation, cost), we will perform descriptive statistics that will summarize: (1) fidelity, i.e. when, how, and what parts of intervention were implemented (child, parent, interventionist report), engagement (child, parent, interventionist report); (2) acceptability, i.e. child/parent satisfaction questionnaire and interview data; (3) implementation, i.e. selection of target stressors, strategies used, barriers identified (interview, session data), rate of booster session completion; and (4) cost, i.e. resources required (session time, additional family contact, booster calls, training/supervision, kit costs). We will consider the intervention feasible if: (i) > 50% of the participants in the intervention group report implementing the intervention; and (ii) > 75% of participants who implemented the intervention report high satisfaction with the intervention. Data on what parts of the intervention were used and the cost will inform future intervention development and research.

To determine the intervention’s efficacy and analyze mechanisms of action and health outcomes, our primary analytic approach will be analysis of covariance (ANCOVA) for initial estimation of effect sizes. ANCOVA can adjust for baseline group differences (intervention versus waitlist) if imbalances occur despite randomization. The dependent variable in each ANCOVA will be a follow-up measure (e.g. T2 adherence, coping; T3 HRQOL, psychological symptoms), with corresponding T1 score as the covariate. Thus, we will examine intervention effects at T2 and T3 while controlling for T1 differences (comparing the intervention group to the waitlist group). We will explore mechanisms of actions at T2 as possible mediators of the intervention effect on health outcomes at T3 via multivariable regression analysis. Data collected at T4 will be exploratory and will also be examined using ANCOVAs to allow us to examine potential intervention timing effects.

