
We recognize a number of potential limitations of this study design. Families may face some barriers to implementing the Cellie Coping Kit, such as difficulty understanding the materials or busy schedules interfering with the intervention. Thus, there may be variation in intervention usage within the intervention and waitlist control groups. We will address this by examining usage per child and parent report; however, the Kit’s portability and child- and parent-driven usage mean that it is not feasible to include behavioral observations to capture actual usage in the child’s environment. Other potential limitations include the possibility of lower than expected retention rates or logistical challenges (e.g. problems contacting participants by phone) that can arise in research with families living in rural communities. Any retention challenges will provide valuable information in planning for future research and intervention implementation. Other limitations of this RCT could include recruitment challenges and potential sampling bias. The research team will work to avoid such challenges by closely monitoring eligibility, recruitment, enrollment, and retention. Strategies will be adjusted as necessary to ensure recruitment goals are met and sample characteristics are reasonably balanced. Given the limited scope and funding for this pilot study, blinding will be limited; research staff and participants will be blind through the baseline assessment but not at subsequent follow-up assessments. To mitigate bias, research staff will be trained to follow a structured protocol to ensure all follow-up assessments are conducted in a similar manner. Because the medical team may directly observe intervention materials, it is not feasible to keep them blinded from study condition. Finally, this research design is a pilot study; thus, future research with a larger sample will be necessary to fully explore intervention effects.

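### The T3 ANCOVAs of the repeated family-reported measures are complete-case and leave out T2 scores already collected, so loss after T2 that works differently in the two arms would bias the effect sizes

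*Protocol article*

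**What the plan says.** The Data analysis section of the protocol article fixes two rules.

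- **Missing data.** "Missing data will be imputed in cases in which at least 50% of a measure’s subscale is complete". With more than half of a subscale's items missing, the participant "will be dropped from analyses requiring those subscales but will be retained in the overall study".
- **Model.** For efficacy, "our primary analytic approach will be analysis of covariance (ANCOVA) for initial estimation of effect sizes". Each ANCOVA takes one follow-up measure at one visit and adjusts for its T1 score. Age, sex and injury characteristics enter all analyses. No T2 score enters a T3 model.

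The Sample size section plans on "40 per condition; 68 [85%] retained to T3", and the Discussion accepts "the possibility of lower than expected retention rates". Study design and Table 1 show HICUPS, PSCQ, PedsQL, PSC and CATS at T1, T2 and T3. Physical recovery is rated only at T3 and adherence is reported only at T2.

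**The concern.** Together the two rules make the T3 comparisons of the repeated family-reported measures complete-case. The T2 score of a child lost after T2 is probably the best available guide to the missing T3 score, and it is set aside.

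This would not matter if loss were unrelated to how the child was doing at T2, or related in the same way in both arms. Here a difference between arms is plausible. Families know their arm after baseline and the follow-up assessors are unblinded. The intervention arm gets an in-person session and the offer of two booster calls, while the waitlist arm gets standard care until after T3.

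What is at stake is the quantity the pilot is meant to deliver: "A goal of this pilot RCT is to estimate effect sizes for a full-scale RCT". A shifted effect size would carry into the design of the next trial.

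**Working it through.** **1. The plan's own figure.** The claim is that the sample "can detect a 0.7 effect size between groups at T3 (ANCOVA) with 80% power and α = 0.05". With 80 × 0.85 = 68 children, or 34 per arm, and a two-sided test (sidedness is not stated), the noncentrality is 0.7 × √(34/2) = 2.886. Power is 81.2% by noncentral t on 66 df and 82.3% by the normal approximation. The stated 80% reproduces and is not in dispute.

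**2. Assumptions for the check.** The documents give no correlations and no dropout mechanism, so these are assumed. Outcome SD is 1, and loss after T2 follows a logistic model with slope ±1 log-odds per SD of the T2 score.

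- Set A: correlations T1–T2 0.5, T1–T3 0.4, T2–T3 0.7; true effect −0.30 (lower is better).
- Set B: correlations 0.5, 0.5, 0.7; true effect +0.70 (higher is better).

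**3. First-order size of the shift.** If loss in one arm depends on T2, the T3 mean of that arm's completers, given T1, moves by about

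slope × p × (ρ23 − ρ12·ρ13),

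where p is the fraction lost.

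- Set A: 1 × 0.15 × (0.7 − 0.5 × 0.4) = 0.075.
- Set B: 1 × 0.15 × (0.7 − 0.5 × 0.5) = 0.068.

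Opposite dependence in the two arms doubles these to 0.15 and 0.135. The approximation runs slightly high.

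**4. Simulation.** With at least 600,000 children per scenario, complete-case T3 ANCOVA on T1 was compared with a likelihood estimate that also uses T2. Loss is 15% and every lost child has T2 data.

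| Loss depends on | Set A, true −0.30: complete-case | Set A: using T2 | Set B, true 0.70: complete-case | Set B: using T2 |
|---|---|---|---|---|
| T2, waitlist arm only | −0.23 or −0.37, by sign | −0.30 | 0.64 (poor status lost) | 0.70 |
| T2, intervention arm only | not run | not run | 0.77 (poor status lost) | 0.70 |
| T2, opposite directions by arm | about −0.17 or −0.43 | −0.30 | 0.83 | 0.70 |
| T2, same in both arms | −0.30 (15% lost in each arm) or −0.28 (15% overall) | −0.30 | 0.67 (15% overall) | 0.70 |
| T1 only, or nothing | −0.30 | −0.30 | 0.70 | 0.70 |

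The arm-specific shifts are therefore about 0.06–0.07 SD when one arm is affected and 0.13–0.14 SD when the directions are opposite. Under a true null, set B gives a spurious 0.06 (one arm) or 0.13 (opposite directions), against 0.00 using T2. At 30% loss the set B shifts are 0.11–0.12 and 0.24.

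**5. Where using T2 helps less** (set A, 15% loss, waitlist-only dependence, true −0.30).

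- Half of the lost children also missed T2: −0.23 becomes −0.27.
- All of them missed T2: −0.24 stays −0.24.
- Loss driven by the unseen T3 value: about −0.18 becomes about −0.22 to −0.23.

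**6. Precision.** At N = 80 with 15% random loss, the SD of the estimate is 0.212 complete-case and 0.204 using T2; 0.204/0.212 = 0.96, a gain of about 4%.

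**7. Consequence for the next trial.** Sample size varies as 1/d². Reading 0.37 for 0.30 gives (0.30/0.37)² = 0.66, about a third too few. Reading 0.23 gives (0.30/0.23)² = 1.70, about 70% too many. On the plan's own 0.7 the effect is milder: (0.70/0.77)² = 0.83 and (0.70/0.64)² = 1.20.

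**The case against.** - **It is a scoring rule.** The text speaks of items within a subscale, and the treatment of missed visits may sit in an analysis plan that is not shown. That is a fair reading of the rule's purpose. But a missed visit meets the stated condition, the single-visit model with T1 only is fixed in the same section, and the power claim counts only the 68 retained. The complete-case result follows from what is written.
- **Not every T3 comparison is affected.** A reader might infer that a child who misses T3 leaves all of them. The document does not support that. The physician's recovery rating comes from record review, and child and parent reports are separate instruments, so losing one need not lose the other. This objection stands and limits the point.
- **Bias is not automatic.** A reader might infer that any link between dropout and the child's condition biases ANCOVA. It does not: dependence on T1 is handled by the adjustment, and a common mechanism does little. The opposite-direction case marks the outer end of the range, and nothing in the document points to it. This stands.
- **The correction is built into the simulation.** Full recovery of the true effect assumes that every lost child gave T2 data and that loss depends only on T2. The document gives retention to T3 only, so neither is known. This stands.
- **The shift is small beside sampling error.** The 95% half-width is about 1.96 × 0.212 = 0.42, well above 0.14. True, but bias that data already in hand could reduce is still worth removing from an estimate meant for planning.

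**Conclusion.** The concern holds in a limited form. By its stated rules the plan analyses HICUPS, PSCQ, PedsQL, PSC and CATS at T3 on completers only and makes no use of their T2 scores. If loss after T2 depends on T2 status differently by arm, the T3 effect moves by roughly 0.06 to 0.14 SD at 15% loss, in either direction. The size rests on assumed correlations of 0.4 to 0.7 and a dropout slope of 1 log-odds per SD; other values would change it.

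The documents do not show that such dropout will occur. They show only that it is plausible, and the power statement is sound. This is an improvement that should be made to the analysis, not a flaw that invalidates the trial.

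**What to change.** For each outcome measured at T1, T2 and T3, replace the separate visit-wise ANCOVAs by one likelihood-based repeated-measures model that includes all randomised children with any data. A suitable form takes T1, T2 and T3 as responses, with baseline means constrained equal between arms, arm-by-visit effects, an unstructured covariance and the planned covariates. Read the T2 and T3 contrasts from it. Multiple imputation using T1 and T2, followed by the planned ANCOVA, is an acceptable alternative. Keep the half-complete rule for scoring subscales, and report the complete-case ANCOVA as a sensitivity analysis.

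State the limits alongside. The change does not reach physical recovery (T3 only) or adherence (T2 only), gives no gain for children who also missed T2, and only partly corrects loss driven by unseen T3 values.

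The cost is revised analysis wording and a little more programming. No extra visits, data or participants are needed. The gain is mainly protection against bias, since the standard error falls by only about 4%.

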Following caregiver consent and child assent, participants will complete a baseline assessment (T1) including measures of coping, HRQOL, and psychological symptoms. Families will then be randomized to the immediate Cellie Intervention (*n* = 40) or Waitlist control (n = 40). Those in the intervention condition will begin the intervention immediately: Cellie interventionists (trained research assistants [RAs]) will meet with families, explain the purpose of the intervention, and provide an overview of the intervention materials. Interventionists will then work with families to identify their three most pressing injury-related challenges, determine which information is most relevant, and help families role-play using these strategies. At two and four weeks after baseline, families in the intervention group will be offered a booster session via phone to discuss use of the Kit, problem-solve difficulties, and apply the Kit to new stressors. Families requiring more intensive support will be referred to other services, as this intervention is not a substitute for psychological treatment. Participants assigned to the waitlist group will receive standard care until they are given access to the Cellie Coping Kit intervention (via mail) after the T3 assessment. Standard care will include family-centered medical care, access to support from child life specialists, and referrals to a social worker, psychologist, and/or psychiatrist if the medical team has concerns about a child’s emotional health. At T3, participants will be provided written instructions on how to use the coping kit (rather than an in-person introduction) and contact information for questions related to the intervention. This group will not receive the booster sessions. Interventionists will complete fidelity measures at T1, booster sessions, and T2 (see Table 1). At 6 weeks (T2), 12 weeks (T3), and 18 weeks (T4) after baseline, participants will repeat T1 measures. In addition, parents will report on adherence at T2 (see Table 1). Children, parents, and a physician (blinded to participants’ condition) will also rate physical recovery at T3. Assessments will be completed via phone or Redcap [43]. It is estimated that participants will complete T1 assessments in approximately 25 min and follow-up assessments in about 20 min. To improve retention, families will be contacted five times each via phone for follow-up assessments. If research assistants are unable to contact families for follow-ups via phone, an electronic link to the follow-up survey on REDCap will be sent via email. If the family does not complete assessments via phone or Redcap [43], families will be asked to complete assessments via mail. The study protocol has been reviewed and approved by the Institutional Review Board at the University of Kentucky and is registered at clinicaltrials.gov. See Fig. 2 for CONSORT diagram [44] and Fig. 3 for the SPIRIT checklist and Addiitional file 1 for SPIRIT checklist.

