
**Table 1 Tab1:** Constructs and measures for RCT

Construct/Measure	Assessment^a^			
Interventionist Report	T1	T2	T3	T4
Fidelity/Fidelity checklist	X (intervention group)	X (intervention group)		
Injury and treatment characteristics/Medical record review/abstraction	X			
Physician report	T1	T2	T3	T4
Physical Injury Recovery			X	
Child Self-Report	T1	T2	T3	T4
Intervention feasibility/Satisfaction Questionnaire [45, 46]		X (intervention group)		X (waitlist group)
Physical Injury Recovery			X	
Coping/How I Coped Under Pressure Scale (HICUPS) [47]	X	X	X	X
Health-related quality of life/Pediatric Quality of Life Inventory (PedsQL) [48]	X	X	X	X
Child and Adolescent Trauma Screen (CATS) [54]	X	X	X	X
Parent Self-Report	T1	T2	T3	T4
Intervention feasibility/Satisfaction Questionnaire [45, 46]		X (intervention group)		X (waitlist group)
Physical Injury Recovery			X	
Adherence/Health Care Questionnaire (HCQ)		X		
Coping Assistance/Parent Socialization of Coping Questionnaire (PSCQ) [47]	X	X	X	X
Health-related quality of life/PedsQL [49, 50]	X	X	X	X
Child Psych Symptoms/Pediatric Symptom Checklist (PSC) [51–53]	X	X	X	X
Child and Adolescent Trauma Screen- Caregiver Report (CATS) [54]	X	X	X	X

^a^Time of assessment: T1 = baseline; T2 = 6 weeks; T3 = 12 weeks; T4 = 18 weeks

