#### Coping and assistance

The How I Coped Under Pressure Scale (HICUPS) [47] will assess the child’s use of adaptive coping strategies with regard to his or her injury and recovery. HICUPS has well-established reliability and validity. Due to the length of the scale, only specific subscales which correspond to content covered in the Cellie tool will be administered.

The Parental Socialization of Coping Questionnaire (PSCQ) [47] will assess parental (caregiver) coaching of child’s coping strategies specific to injury-related stressors. The measure parallels the HICUPS child measure described above, but parents are asked to rate the extent to which they have encouraged versus discouraged each specific child-coping strategy. Reliability and validity of the measure have been established. Due to the length of the scale, only specific subscales which correspond to content covered in the Cellie tool will be administered.

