#### Health-related quality of life

The Pediatric Quality of Life Inventory (PedsQL) [48] is a well-validated measure of child HRQOL. It is developmentally appropriate, with child self-report and parent-report instruments available for ages 2–18 years. The PedsQL has four scales with a total of 23 items: Physical health / physical functioning (eight items); Psychosocial health / emotional functioning (five items); Psychosocial health / social functioning (five items); and Psychosocial health / school functioning (five items).

The PedsQL Caregiver Report [49, 50] consists of 23 items and parallels the child-report PedsQL above. This measure has well-established psychometric properties [49, 50].

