Building on promising findings from pilot studies [25], the current RCT goals represent an important next step in the advancement of the Cellie Coping Intervention for Injury. The strengths and potential positive outcomes of implementing a waitlist control RCT design with multiple informants are numerous. The current study design obtains data from both the child and parent perspective on physical recovery, emotional recovery, and response to the intervention. In addition, the design includes the physicians’ perspective on physical recovery and Cellie interventionists’ perspectives on intervention engagement / uptake. Combining data from multiple informants will provide rich information specific to the targets (i.e. adherence, coping behaviors, physical recovery, emotional health, HRQOL) and intervention engagement. Collecting data on cost, and on engagement from multiple perspectives (child, parent, and interventionist), will lay the ground work for more research on intervention dissemination and implementation. The longitudinal study design will allow us to examine change over time and investigate both short- and long-term effects of the intervention. Evaluating the level of support that a family needs to implement the Cellie Intervention is also a study strength. The role of the interventionist in this intervention has been designed so that advanced credentialing (i.e. licensure or certification) is not necessary. Rather, a wide range of health and behavioral healthcare workers can be trained to teach and support the use of the Cellie Coping Kit, facilitating implementation and sustainability of the approach. This is especially important in many rural healthcare professional shortage areas, where professionals with advanced degrees are in short supply, yet high demand. The design of this study will allow us to explore whether Cellie interventionists are necessary (Cellie intervention group) or whether the family can use the intervention with no additional instruction (waitlist group). The use of a waitlist control group will allow group comparisons at T2 and T3, with the additional possibility of examining intervention timing effects at T4. In addition, the waitlist design ensures that all participants will be offered the Cellie Coping Kit for Injury intervention addressing the overarching goal of the team to provide evidence-based resources to promote injury recovery. The target population of this study is also a strength. Much research on adherence/health to date has been conducted with chronic illness populations rather than injury [32–34]. Injury is in many ways qualitatively distinct from other health conditions in its treatment and long-term physical and emotional impact. In addition, this research protocol will include many families from rural communities, an underserved and under-researched population [62]. Including several strategies of collecting follow-up data (via phone, Internet, mail) will contribute to our understanding of how to engage and retain participants from rural communities at follow-up time points.

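### The exploratory mediation analysis does not separate informants, so a link between a T2 mechanism and a T3 outcome reported by the same unblinded parent or child may reflect shared reporting

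*Protocol article*

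**What the plan says.** The Data analysis section of the protocol article gives mediation one sentence: "We will explore mechanisms of actions at T2 as possible mediators of the intervention effect on health outcomes at T3 via multivariable regression analysis". No informant is named and no pair is excluded.

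Table 1 and the measure descriptions fix who reports what:

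- **Adherence (HCQ):** parent only, and only at T2 ("In addition, parents will report on adherence at T2"), so it has no T1 score.
- **Coping assistance (PSCQ):** parent only, T1 to T4. It "will assess parental (caregiver) coaching of child’s coping strategies specific to injury-related stressors".
- **Child coping (HICUPS):** child only, T1 to T4. It "will assess the child’s use of adaptive coping strategies with regard to his or her injury and recovery".
- **T3 outcomes:** PedsQL and CATS come from child and parent; the caregiver PedsQL "consists of 23 items and parallels the child-report PedsQL above". Physical recovery is rated by child, parent and a physician blinded to condition. The PSC is parent report only.

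The Discussion states that participants are blind through the baseline assessment but not at follow-up. It also counts the several informants as a strength ("Combining data from multiple informants will provide rich information specific to the targets") without saying how their reports will be combined.

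**The concern.** The parent leads the intervention, knows the allocation and is the only source for two of the three mechanism measures. The child also knows the allocation and is the only source for the third. Anything that colours one person's answers at both T2 and T3 (expectation, mood, a wish to have done well) enters mediator and outcome together and raises the mediator-outcome coefficient. Adjusting for T1 scores cannot remove a component that arises after T1, and adherence has no T1 score to adjust for.

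Changing the mechanisms of action is the second of the three objectives in the Current study section, and the pilot is meant to inform a full-scale trial. A mechanism that is only a shared respondent could be carried forward as the one to build on.

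**Working it through.** **The plan's own figure.** 80 × 0.85 = 68 retained, or 34 per arm. A two-sample t-test with d = 0.7 and two-sided α = 0.05 has 81.2% power and a detectable effect of 0.69, so the stated 80% is reproduced. The article gives no figure for mediation.

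**Which pairs the sentence admits at T3**

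| Mediator (reporter) | PedsQL, CATS | PSC | Physical recovery |
|---|---|---|---|
| HCQ, PSCQ (parent) | same or cross (child) | same only | same, cross (child), or blinded physician |
| HICUPS (child) | same or cross (parent) | cross only | same, cross (parent), or blinded physician |

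Three of the four outcomes have a second informant.

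**Model.** The documents give n = 68. The rest is assumed: a T1-to-follow-up correlation of 0.5 (residual variance 1 − 0.5² = 0.75), a true kit effect a on the mediator, and no true mediator-outcome effect. A reporter component of SD s, arising after T1, is added to each score. Mediator and outcome components correlate c: 1 for the same informant, 0 for independent informants, and 0.5 if parent and child biases are partly shared.

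After adjustment for arm and both T1 scores, each residual variance is 0.75 + s² and their covariance is c·s². The spurious coefficient, which is also the partial correlation r, is c·s² / (0.75 + s²). For c = 1:

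- s = 0.3: 0.09 / 0.84 = 0.107
- s = 0.4: 0.16 / 0.91 = 0.176
- s = 0.6: 0.36 / 1.11 = 0.324

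With a = 0.7 the spurious indirect effects are 0.7 × these: 0.075, 0.123 and 0.227.

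**Probability of joint significance.** With P(d) = Φ(d − 1.96) + Φ(−d − 1.96):

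- Mediator-outcome path: d = atanh(r) × √(68 − 3 − 3) = 0.85, 1.40, 2.65, so P = 0.135, 0.288, 0.755.
- Arm-mediator path, a = 0.7: d = 0.7 / √[(0.75 + s²) × 2/34] = 3.15, 3.03, 2.74, so P = 0.883, 0.857, 0.782.
- Arm-mediator path, a = 0.3: P = 0.271, 0.254, 0.217.

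Multiplying the two paths, against simulation of the same kind of model:

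| Setting | Formula, s = 0.3 / 0.4 / 0.6 | Simulated |
|---|---|---|
| Same informant, a = 0.7 | 12% / 25% / 59% | 11% / 24% / 57% |
| Same informant, a = 0.3 | 4% / 7% / 16% | 3% to 15% |
| Cross-informant, independent, a = 0.7 | 4% / 4% / 4% | about 4% |
| Cross-informant, independent, a = 0.3 | 1% / 1% / 1% | not listed |
| Cross-informant, c = 0.5, a = 0.7 | 6% / 9% / 20% | 6% to 18% |

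**Adherence, with no T1 mediator score.** The mediator's residual variance becomes 1 + s², so r = s² / √[(1 + s²)(0.75 + s²)] = 0.094, 0.156, 0.293. At a = 0.7 this gives 9%, 18% and 47% (simulated: 8%, 19%, 48%).

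**A different scenario.** Suppose the kit changes nothing, but intervention families shift their reports by 0.5 SD and 20–40% of score variance belongs to the reporter (all assumed). Simulated same-informant false mediation is 14–46% without a T1 mediator score and 24–60% with one. Over shifts of 0.3 to 0.7 SD the same-informant range is 7–82%, and cross-informant pairs, run without a T1 mediator score, give about 1–4%. With no reporter variance, same-informant pairs stay at 1–5%.

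**The case against.** **The text does not commit to same-informant pairs.** A reader might infer that the analysis will pair measures from one reporter. The document does not say so: it leaves the pairing open, and cross-informant pairs can be formed from what is collected. Only HCQ or PSCQ with PSC is forced. This part of the objection stands.

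**Pairing is detail for a fuller plan, and the analysis is exploratory.** The article uses the language of exploration, makes ANCOVA the primary approach and says a larger sample is needed to explore effects fully. That limits the weight of the point. It does not remove it, because the stated rule covers all mechanisms and outcomes and so admits pairs that cannot tell mediation from shared reporting.

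**The size depends on assumptions.** This stands. The reporter SD is not in the document. The 0.7 in the Sample size section is an effect detectable at T3, not an expected T2 effect on the mediator. At 0.3 SD most of the range is modest.

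**Cross-informant pairing is no cure and has a price.** This also stands. Parent and child are both unblinded and use the kit together, so their biases may correlate. Only the physician is condition-blind, and that rating is a 3-point judgement from the medical record, covering physical recovery only. With a true mediator-outcome coefficient of 0.3 and independent reporters, simulated cross-informant joint significance was only 46%, 40% and 28% at s = 0.3, 0.4 and 0.6. Barring same-informant pairs from any mechanism claim would therefore go too far.

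**Conclusion.** The point holds as a weakness in how the mediation analysis is framed. The sentence admits same-informant pairs, forces them for HCQ or PSCQ with PSC, and T1 adjustment does not remove reporter variance that arises later. Under shared SDs of 0.3 to 0.6, false joint significance is about 11–57% at a kit effect of 0.7 SD on the mediator and about 3–15% at 0.3 SD. Cross-informant pairs give about 1–4% with independent biases and about 6–18% (at 0.7 SD) when biases correlate 0.5. The direction is the same under both scenarios examined; the size rests on assumed values.

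The documents do not support the stronger reading that any mediation found will be spurious. That would require knowing the size of the shared reporter component and of the kit's effect on the mediator or on reporting, and none of these is given.

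**What to change.** Add to the Data analysis section, after the mediation sentence, that each T2 mediator will also be tested against the T3 outcome from a different informant wherever one is collected:

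- HCQ and PSCQ with child-reported PedsQL and CATS, and with the blinded physician's recovery rating.
- HICUPS with parent-reported PedsQL, CATS and PSC, and with the blinded physician's recovery rating.

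Report these beside the same-informant pairs, naming the informant for each. State in advance that a mediation signal seen only in same-informant pairs, including every HCQ-to-PSC and PSCQ-to-PSC path, will be described as possibly due to shared reporting.

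The cost is wording and a few more exploratory models; every measure is already in Table 1. Cross-informant associations are weaker, so fewer signals will appear. The change reduces the bias without removing it, because both family reporters are unblinded.
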